#### Blinding

Outcome adjudicators alone will be blinded to intervention assignment. When recording the assessment task video, desk surfaces will be covered with plain white paper, and participants will not be visible above the elbow. Video files will be renamed and reordered through random number generation prior to adjudicator review.

### Data Collection, Management, and Analysis

#### Data Collection

Applicants will complete a questionnaire that elicits personal data, which will be used for correspondence. Participants will complete a questionnaire immediately before and after the intervention. All questionnaires will be administered using Jisc Online Surveys [13]. Participants will record the assessment tasks by using a personal device with an integrated camera. Framing specifications will be provided in advance. Video files will be shared with trial coordinators securely via WeTransfer [14].

#### Data Management

All data will be stored on encrypted hard-drives under password protection. Personal data collected from applicants will be accessed by trial coordinators only to permit the collection of nonidentifiable information from participants. Participants will be assigned anonymous numeric IDs, which will be used to identify their video recordings and questionnaire responses.

#### Statistical Methods

Within-group proficiency improvements after the interventions will be analyzed using the dependent *t* test. Between-group postintervention proficiency will be assessed through analysis of covariance with baseline proficiency as a covariate in the regression model. Post hoc analysis will be performed using the Fisher test of least significant difference. The combined hypothesis that VCT is both superior to CBL and noninferior to FFT will be tested at a 95% significance level. The noninferiority margin (*δ*) was defined on the basis of historical data. An observational study investigated the effect of FFT on OSAT scores, with a reported difference of 3.7 (95% CI 2.7-4.7) in mean values [15]. A *δ* of 0.675 was selected to ensure a preserved fraction of 3/4.

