**Results:**

The primary outcome will be the postintervention Objective Structured Assessment of Technical Skills score, adjudicated by 2 experts blinded to the study and adjusted for baseline proficiency. The noninferiority margin (*δ*) will be defined using historical data.

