#### Outcomes

Baseline characteristics will be collected to facilitate the identification of systematic differences between intervention groups that may increase the risk of bias. Age, year group, sex, and hand dominance will be elicited through a preintervention questionnaire. The primary outcome will be postintervention suturing and hand-tying proficiency, adjusted for preintervention proficiency. After the initial instructional video and again immediately after the intervention, participants will complete an assessment task. The task will include placing 3 interrupted sutures with hand-tied knots by using a single silk suture, with a time limit of 4 minutes. Proficiency will be measured using a validated Objective Assessment of Surgical and Technical Skills (OSAT) used by the Royal College of Surgeons [10]. Scores will be adjudicated by 2 experts blinded to the study design. Proficiency will be defined as the mean value of both adjudicator scores.

Secondary outcomes will be the students’ subjective suturing and knot-tying confidence, perceptions of the intervention, and expenses associated with session attendance. Subjective confidence and perceptions will be elicited through a postintervention questionnaire and measured on a 5-point Likert scale. Expenses will be self-reported by participants.

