#### Sample Size

The effect of VCT on OSAT-measured proficiency is not reported in the existing literature. The VCT technology implemented by this trial has been optimized for 24 attendees. A total sample size of 72 individuals (n=24 per intervention group) was therefore selected. A sensitivity power analysis was performed using a 2-tailed dependent samples *t* test. With an *α* and *β* error probability of .05, a minimum detectable effect of 0.769 was computed.

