### Assignment of Interventions

#### Allocation

A web-based questionnaire will be distributed to the participants to elicit their subjective confidence in their own suturing ability and the quantity of formal (expert-led) and informal (peer-led or independent) suturing training they have previously received. Participants will then be stratified by subjective suturing confidence—measured on a 5-point Likert scale—and objective previous suturing training experience—measured to the nearest hour. Permuted block randomization (block size=3) will be carried out to allocate the participants within each stratum to 1 of the 3 intervention groups. Permutations will be selected by a random number generator. Comprehensive instructions and guidelines to be followed before and during the training sessions will also be provided. Participants who do not want or are unable to participate will be replaced through random selection from the remaining list of applicants where possible.

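### The stated primary ANCOVA omits the two randomisation factors; adding them costs 2 df and narrows the interval if they explain more than about 3% of residual variance

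*Protocol article*

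**What the plan says.** **Allocation.** "Participants will then be stratified by subjective suturing confidence", rated on a five-point Likert scale, and by "objective previous suturing training experience—measured to the nearest hour". Within those strata, "Permuted block randomization (block size=3) will be carried out to allocate the participants within each stratum". Both factors come from a questionnaire completed before allocation.

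**Analysis.** Statistical Methods gives the between-group model as "analysis of covariance with baseline proficiency as a covariate in the regression model". Two other places agree. Outcomes: "The primary outcome will be postintervention suturing and hand-tying proficiency, adjusted for preintervention proficiency". Abstract, Results: "adjudicated by 2 experts blinded to the study and adjusted for baseline proficiency".

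**Size.** Sample Size: "A total sample size of 72 individuals (n=24 per intervention group) was therefore selected".

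Neither stratification factor appears in the stated model, and no reason is given for leaving them out.

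**The concern.** Stratified allocation makes the arms more alike on the stratification factors than simple randomisation would. If those factors predict the outcome, a model that ignores them leaves their contribution in the residual. Where stratification did balance the arms, the model-based standard error is then larger than the true sampling variability. Where it did not, the leftover imbalance adds real noise to the estimate.

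Both apply here. A grid of five confidence levels by whole hours, filled by 72 people in blocks of 3, will have many sparse cells and incomplete blocks. Precision matters because the trial must show superiority to one arm and noninferiority to the other with 24 per arm and a margin of 0.675 OSAT points.

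**Working it through.** **1. The protocol's own figures.** The minimum detectable effect of 0.769 (Sample Size) reproduces: a paired t test with n = 24, df = 23, two-sided alpha 0.05 and power 0.95 gives 0.7688. The margin (Statistical Methods) also reproduces: a preserved fraction of 3/4 of the lower confidence limit 2.7 leaves 0.25 × 2.7 = 0.675. Neither depends on the covariates, so neither shows what adjustment is worth.

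**2. Net effect on interval width.**
- The stated model has an intercept, two arm terms and baseline OSAT: 72 − 4 = 68 residual df. Two more terms leave 66.
- Let R² be the share of residual variance, after baseline OSAT, that the two factors explain. It is assumed, because the documents do not give it.
- Expected half-width ratio, extended to stated model = [t(0.975, 66) / t(0.975, 68)] × √(67/65) × √(1 − R²) = (1.9966/1.9955) × 1.0153 × √(1 − R²) = 1.0158 × √(1 − R²). The factor 67/65 is the average price of estimating two more coefficients.

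| Assumed R² | Half-width ratio | Equivalent N = 72/ratio² |
|---|---|---|
| 0 | 1.016 | 69.8 |
| 0.02 | 1.006 | 71.2 |
| 0.05 | 0.990 | 73.5 |
| 0.10 | 0.964 | 77.5 |
| 0.20 | 0.909 | 87.2 |

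Break-even: 1 − 1/1.0158² = 0.031, about 3%. With 5 df instead (four Likert dummies plus hours), the ratios at R² = 0, 0.05, 0.10 and 0.20 are 1.041, 1.015, 0.988 and 0.931, so linear coding is the better bargain.

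**3. Simulation of the allocation scheme.** There were 4,000 runs per setting with 72 participants, strata formed by Likert level × whole hours, and blocks of 3. The factor distributions and a correlation of 0.5 between the factors and baseline OSAT are assumptions. The outcome was generated as linear in confidence and log(1+hours), which favours the extended model.
- On average about 26 strata were occupied, and about 28 participants sat in incomplete blocks.
- The SD of the between-arm difference in the combined factors was 0.202, against √(2/24) = 0.289 under simple randomisation. Thus 0.202/0.289 = 70% of chance imbalance remained.

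| Assumed R² | Type I error, stated model | Type I error, extended model | Half-width ratio, extended/stated |
|---|---|---|---|
| 0 | 0.052 | 0.051 | 0.5861/0.5809 = 1.009 |
| 0.05 | 0.047 | 0.051 | 0.5713/0.5809 = 0.983 |
| 0.10 | 0.045 | 0.051 | 0.5561/0.5811 = 0.957 |
| 0.20 | 0.041 | 0.051 | 0.5243/0.5816 = 0.901 |

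Nominal two-sided error is 0.05, and Monte Carlo error is about 0.0035. The ratios are slightly better than in step 2 because stratification balances the factors in part.

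**4. The two mechanisms, at R² = 0.20.** In the stated model the mean standard error was 0.5816/1.9955 = 0.2915, against an actual SD of the estimate of 0.2839: an overstatement of 2.7%. The actual SD was itself 0.2839/0.2640 = 1.075 times that of the extended model. Most of the loss is real noise from remaining imbalance; the smaller part is an overstated standard error.

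**5. Against the margin.** The half-width under the stated model is 1.9955 × √(2/24) = 0.576 residual SDs, taking a two-sided 95% interval. The documents give no SD. With no true difference, noninferiority power under the stated model, and with R² = 0.10 or 0.20 under the extended one, is 63.5%, 66.7% and 71.8% for an assumed SD of 1 point, and 21.0%, 22.3% and 24.5% for an SD of 2.

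**The case against.** **Baseline OSAT may already carry the information.** It is measured on the same task, after the instructional video and before the intervention, so it directly measures the skill for which confidence and hours are proxies. R² could be small, and below about 3% adjustment gains nothing. This stands, and it is why the gain is given as a range. It also rules out saying that imbalance is left wholly uncorrected. Against it, baseline OSAT comes from one task with a four-minute limit and so carries measurement error.

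**The stated analysis is valid.** This stands. A reader might infer that omitting stratification factors biases the comparison or invalidates the test. The omission does not bias the estimate, and simulated error rates sit at or below nominal within Monte Carlo error. A conservative test does not raise the risk of a false noninferiority claim.

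**The gain rarely decides the result.** At R² = 0.10 the half-width falls from 0.576 to 0.555 SD. It drops below 0.675 because of adjustment only if the residual SD lies between 0.675/0.576 = 1.17 and 0.675/0.555 = 1.22 points. This stands as a limit on importance, though power rises modestly at other SDs too.

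**Sparse strata and overstated standard errors pull in opposite directions.** Only in part. Better balance means more overstatement and less real noise, but both are contained in the same excess width, and adjustment addresses both.

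**The article is condensed, and the factors' purpose is not stated.** The protocol gives no reason for choosing these factors, so their prognostic value is an inference. A fuller model may exist elsewhere. But three places name the same single adjustment, so this is a stated model that does not match the allocation, not silence.

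**Conclusion.** The mismatch is in the text: allocation uses confidence and training hours, and the stated primary model uses neither. It is a moderate point about efficiency and consistency with the design, not a flaw that invalidates the trial. Its size depends on an unknown R²: net of degrees of freedom, the interval changes by about +1.6%, −1.0%, −3.6% or −9.1% at R² of 0, 0.05, 0.10 or 0.20. The last three are worth about 1.5, 5.5 and 15 participants.

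Two stronger readings are not supported:
- A reader might use √(1 − R²) alone and claim reductions of 2.5%, 5% and 11% (4, 8 and 18 participants). That ignores the cost of the added terms.
- A reader might extend the point to the secondary confidence outcome. Of that outcome the protocol says "Subjective confidence and perceptions will be elicited through a postintervention questionnaire", but it states no model for it, so there is nothing to contradict. Nor are the two ratings shown to be the same item: the allocation questionnaire asks about confidence in suturing, the outcome about suturing and knot-tying.

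**What to change.** Before analysis, amend the primary between-group model to: post-intervention OSAT on arm, baseline OSAT, pre-allocation confidence (1 to 5, one linear term) and log(1+hours of previous training), using the same values that formed the strata. Do not fit one dummy per stratum; with about 26 occupied strata (simulated) that would take about 25 df from 72 participants. If the sponsor prefers the present model, the protocol should say why the factors are left out.

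The cost is one line, 2 df, and on average an interval about 1.6% wider if neither factor is prognostic. No new data are needed, because both factors are collected before allocation. Data collection has started, but the Protocol Amendments section provides for describing and justifying statistical changes in an updated protocol. Fixing the covariates now also avoids choosing them later in response to an observed imbalance.

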### Objectives

This trial is designed to assess the effect size of the 3 interventions and test both the superiority of VCT to CBL and its noninferiority to FFT. We hypothesize that the efficacy of VCT will be greater than that of CBL and similar to that of FFT. We also aim to assess and compare the feasibility and accessibility of the 3 training modalities.

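### The combined hypothesis is given a 95% significance level, which is not an alpha, and the only pairwise procedure named is post hoc Fisher LSD rather than the two planned ANCOVA contrasts

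*Protocol article*

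**What the plan says.** All of this is in the protocol article. Under Objectives, the trial is to "test both the superiority of VCT to CBL and its noninferiority to FFT". Under Statistical Methods, the between-group model is an ANCOVA: "Between-group postintervention proficiency will be assessed through analysis of covariance with baseline proficiency as a covariate in the regression model". The next sentence names the pairwise method: "Post hoc analysis will be performed using the Fisher test of least significant difference". Then comes the decision threshold: "The combined hypothesis that VCT is both superior to CBL and noninferior to FFT will be tested at a 95% significance level". The section closes with the margin, derived from a historical FFT effect "with a reported difference of 3.7 (95% CI 2.7-4.7) in mean values"; a value "of 0.675 was selected to ensure a preserved fraction of 3/4".

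The section does not mention an omnibus F test, does not say that the combined hypothesis is tested through LSD, and does not say how the margin is compared with the ANCOVA estimate.

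**The concern.** There are two faults in what the text states.

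- **The threshold.** A significance level of 95% is not a usable alpha. The natural repair is alpha 0.05, or 95% confidence, but that does not fix the sidedness of the noninferiority test. A two-sided 95% interval implies one-sided 2.5%. A one-sided test at 0.05 implies 5%. The second doubles the maximum false-noninferiority rate and moves the line between success and failure.
- **The procedure.** VCT v CBL and VCT v FFT are directional comparisons fixed in advance, yet the only pairwise method named is a post hoc one whose null is no difference. Its p value for VCT v FFT does not address whether VCT is worse by less than 0.675. LSD is also commonly run only after a significant three-group F test. Noninferiority should not depend on evidence that some arms differ. Because both claims must succeed (an intersection-union test), no omnibus protection is needed.

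At stake are the stated error rate of the noninferiority conclusion and a modest loss of power if an analyst applies LSD in its protected form.

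**Working it through.** **Inputs from the protocol article.** 24 per arm, three arms (Sample Size); margin 0.675, preserved fraction 3/4, historical CI 2.7 to 4.7 (Statistical Methods); two-tailed alpha .05, beta .05, detectable effect 0.769 (Sample Size).

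**Assumption.** The article gives no SD for the OSAT score. The residual SD after ANCOVA is taken as 0.5 to 3 points.

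**1. The article's own figures.** The margin reproduces: (1 - 3/4) x 2.7 = 0.675. The detectable effect reproduces: a paired t test with n = 24, 23 df, two-sided 0.05 and 95% power gives 0.7688. That is a within-group figure. It is used below only as a convenient size for the VCT-CBL effect.

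**2. What the open sidedness does.** The ANCOVA has 72 - 3 - 1 = 68 residual df. The standard error of a two-arm contrast is SD x sqrt(2/24) = 0.2887 x SD. The t quantiles are 1.995 (one-sided 2.5%) and 1.668 (one-sided 5%). At SD 1:

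- One-sided 2.5%: half-width 1.995 x 0.2887 = 0.576, so noninferiority needs an observed VCT-FFT difference above -0.675 + 0.576 = -0.099.
- One-sided 5%: 1.668 x 0.2887 = 0.481, so it needs a difference above -0.675 + 0.481 = -0.194.

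An observed difference between -0.194 and -0.099 would pass under one reading and fail under the other. With VCT truly worse than FFT by exactly 0.675, simulated false noninferiority is about 2.5% under the first reading and about 5% under the second, at SDs from 0.5 to 3.

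**3. What an F gate would do, if applied.** Three arms of 24 were simulated with 68 residual df and 100,000 runs per setting. The rule is that VCT-CBL is significant in favour of VCT at two-sided 0.05 and the lower 95% limit of VCT-FFT lies above -0.675. The truth is VCT = FFT and VCT-CBL = 0.769 SD.

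| Residual SD | Power, no gate | Power, F p < .05 also required | Loss (points) |
|---|---|---|---|
| 0.5 | 74.5% | 68.9% | 5.6 |
| 1 | 54.0% | 48.5% | 5.5 |
| 2 | 20.0% | 18.0% | 2.0 |
| 3 | 11.0% | 10.3% | 0.7 |

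With VCT-CBL = 1.0 SD the loss is under 2 points (SD 1: 61.8% to 60.2%).

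**4. Type I error.** A gate adds a condition to the success rule, so it can only remove successes. With VCT truly 0.675 below FFT and VCT-CBL = 1.0 SD, the margin-based rule wrongly succeeds in about 2.5% of runs, gated or not.

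**The case against.** The strongest reply is that the serious version of this point is not in the text. A reader might infer that a nonsignificant LSD comparison of VCT with FFT will be taken as noninferiority, especially as the Objectives add "We hypothesize that the efficacy of VCT will be greater than that of CBL and similar to that of FFT". The document does not support that. The same section fixes a margin of 0.675, for which a zero-difference test has no use, and the sentence before that hypothesis names noninferiority as what is tested. The high false-success rates that such a misuse would produce therefore do not describe this plan. This part of the reply stands.

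A reader might likewise infer that the combined hypothesis is gated on the omnibus F. That follows only from the usual protected form of LSD; the article writes out no gate. Nor are power losses for VCT v CBL taken alone the right measure, because the claim is the combined one. This stands too.

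It can also be said that an ungated LSD interval is the unadjusted interval from the model's pooled error, and so identical to the contrast interval recommended here; and that protected LSD is defensible for exactly three groups. Both are true. They show that the remedy is small, not that the text is sound: protection over three pairwise comparisons is not needed for a claim that requires two named ones to succeed together.

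Finally, sidedness and interval construction often sit in an analysis plan, which is not shown, and the two-tailed .05 under Sample Size points to a two-sided 95% interval. As an omission, the missing sidedness would be no finding. But the article does state a threshold, and states it wrongly, while the two-tailed .05 belongs to a within-group paired test and does not govern noninferiority.

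**Conclusion.** The point holds in a limited form. The stated threshold is wrong as an alpha and leaves two readings for noninferiority, with maximum false-noninferiority rates of about 2.5% and 5%. Naming post hoc LSD as the sole pairwise procedure does not fit two prespecified contrasts, and its zero-difference p value cannot by itself show noninferiority. If the implied F gate were used, the combined claim would lose about 1 to 6 percentage points of power at a VCT-CBL effect of 0.769 SD, with no inflation of type I error.

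The power figures rest on the assumed residual SD of 0.5 to 3 points, on VCT and FFT being equal in truth, and on 24 analysed per arm. The two stated faults do not depend on the SD. Severity is minor to moderate: the wording should be corrected before analysis, but the document does not commit the trial to an invalid noninferiority test.

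**What to change.** In Statistical Methods:

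- Replace the 95% significance level with one-sided 2.5% for each test, read from two-sided 95% confidence intervals.
- State that both contrasts come directly from the single three-arm ANCOVA. VCT is superior to CBL if the lower limit of VCT-CBL is above 0, and noninferior to FFT if the lower limit of VCT-FFT is above -0.675.
- State that both are required, with no omnibus F test as a precondition and no multiplicity adjustment.
- Label any remaining LSD comparison, such as FFT v CBL, as descriptive.

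The cost is wording only: no change to sample size, data collection or model. The Protocol Amendments section already provides for describing and justifying changes to the statistical plan in an updated protocol. The Results section says data collection has begun and analysis is still to come, so the rule should be fixed before any between-arm result is seen.

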**Objective:**

We aim to investigate whether VCT is superior to computer-based learning and noninferior to FFT in improving proficiency in basic surgical skills.

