**Methods:**

This is a protocol for a parallel-group, noninferiority, randomized controlled trial. A sample of 72 undergraduates will be recruited from 5 medical schools in London. Participants will be stratified by subjective and objective suturing experience level and allocated to 3 intervention groups at a 1:1:1 ratio. VCT will be delivered using the BARCO weConnect software, and FFT will be provided by expert instructors. Optimal student-to-teacher ratios of 12:1 for VCT and 4:1 for FFT will be maintained. The assessed task will be interrupted suturing with hand-tied knots.

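### The single confirmatory claim needs both parts at once; testing them in a fixed order would keep superiority to CBL claimable when noninferiority is missed, at no cost

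*Protocol article*

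**What the plan says.** The protocol article names one hypothesis for the formal test (Statistical Methods): "The combined hypothesis that VCT is both superior to CBL and noninferior to FFT will be tested at a 95% significance level". The margin is 0.675 OSAT points.

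The same section plans the between-group model, "Between-group postintervention proficiency will be assessed through analysis of covariance with baseline proficiency as a covariate in the regression model", followed by pairwise comparisons: "Post hoc analysis will be performed using the Fisher test of least significant difference".

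The aims are worded jointly. The abstract asks "whether VCT is superior to computer-based learning and noninferior to FFT in improving proficiency in basic surgical skills". The Objectives section says the trial will "test both the superiority of VCT to CBL and its noninferiority to FFT", and adds: "We hypothesize that the efficacy of VCT will be greater than that of CBL and similar to that of FFT". The abstract's Methods paragraph labels the design a noninferiority trial.

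The article does not say what may be claimed if only one part succeeds.

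**The concern.** Superiority to CBL and noninferiority to FFT are separate scientific questions with separate uses. A finding that live virtual teaching beats a video matters even if equivalence to classroom teaching stays open. Under the stated rule, a trial that clearly beats CBL but misses the margin fails its only named hypothesis. The VCT-CBL result is then reported as a follow-up comparison without confirmatory standing.

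There is a second risk. Faced with that result, the investigators may wish to claim the successful part anyway. If either part could be claimed alone, with no order and no alpha split, the chance of at least one false claim would exceed the per-test level. The protocol does not plan this, but an order fixed before analysis removes the temptation.

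**Working it through.** **The document's own figures**

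- Margin: a preserved fraction of 3/4 applied to the lower confidence limit of 2.7 gives (1 − 0.75) × 2.7 = 0.675. It reproduces.
- Minimum detectable effect: a two-sided paired t test with n = 24, alpha 0.05 and power 0.95 (noncentral t) gives d = 0.7688, against 0.769 stated. It reproduces. It is a within-group effect, so it says nothing about power for either between-group comparison.

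**Inputs**

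- From the document: 24 per arm (Sample Size); margin 0.675 and ANCOVA with one covariate (Statistical Methods). Residual df = 72 − 3 − 1 = 68.
- Assumed, because not given: residual SD, true VCT-CBL gain, VCT truly equal to FFT, and one-sided 2.5% per part.

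**What each part requires**

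The standard error of a pairwise difference is SD × √(2/24) = 0.289 × SD. The critical value is t(68) = 1.995.

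Example at SD 2: SE = 0.577, and 1.995 × 0.577 = 1.152.

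- Superiority needs an observed VCT − CBL above 1.15.
- Noninferiority needs an observed VCT − FFT above −0.675 + 1.152 = 0.48, so VCT would have to look better than FFT.

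Noninferiority power at true equality falls below 50% once the SD exceeds 1.17 (or 1.40 at one-sided 5%).

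**Outcome patterns** (simulation, 400,000 three-arm trials per row)

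| SD | VCT-CBL gain | Superiority only | Both | Noninferiority only | Neither |
|---|---|---|---|---|---|
| 1 | 1 | 0.310 | 0.618 | 0.017 | 0.056 |
| 1 | 2 | 0.366 | 0.634 | 0.000 | 0.000 |
| 1.5 | 2 | 0.659 | 0.336 | 0.000 | 0.005 |
| 2 | 1 | 0.255 | 0.146 | 0.064 | 0.535 |
| 2 | 2 | 0.719 | 0.208 | 0.002 | 0.072 |
| 3 | 1 | 0.145 | 0.061 | 0.056 | 0.738 |
| 3 | 3 | 0.812 | 0.116 | 0.001 | 0.072 |
| 4 | 1 | 0.098 | 0.036 | 0.047 | 0.819 |
| 4 | 2 | 0.335 | 0.066 | 0.018 | 0.581 |

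Over SD 1.5 to 4 and gains of 2 to 3, superiority alone occurs in 34% to 81% of trials and both parts in 7% to 34%.

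**Error rates when both nulls hold at their boundaries** (VCT = CBL, and VCT below FFT by 0.675)

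The shared VCT arm gives the two statistics a correlation of (1/24)/(2/24) = 0.5. By the bivariate normal:

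| Rule | One-sided 2.5% per part | One-sided 5% per part |
|---|---|---|
| Both required (as planned) | 0.46% | 1.2% |
| Either claimable, no order | 2 × 2.5 − 0.46 = 4.5% | 2 × 5 − 1.2 = 8.8% |
| Fixed sequence, superiority first | 2.5% | 5% |

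The unordered rule runs at about 1.8 times the per-test level (4.5/2.5 = 1.8; 8.8/5 = 1.76).

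**Why the fixed sequence holds its level**

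- If VCT is truly no better than CBL, any false claim must begin with a false rejection at the superiority step, which has probability at most alpha.
- If VCT is truly better than CBL, only the noninferiority claim can be false, again with probability at most alpha.
- Both claims are made exactly when both statistics pass, which is the present rejection region. Power for the combined claim is therefore unchanged.

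At SD 2 and gain 2, the chance of some confirmatory conclusion rises from 0.208 to 0.208 + 0.719 = 0.927.

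**The case against.** The case for leaving the plan alone is substantial, and much of it stands.

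- **There is no contradiction.** A reader might infer that the objectives pose two separate questions and the analysis answers a different one. The abstract, the Objectives section and Statistical Methods can all be read as the same conjunction, and calling the design noninferiority does not say that VCT against FFT alone decides.
- **The conjunction is valid.** Each part runs at full alpha without adjustment. A reader might infer that partial success leaves no valid conclusion. It leaves one: the combined hypothesis was not shown.
- **VCT against CBL is analysed.** ANCOVA with least-significant-difference comparisons will produce it. With three groups and an omnibus gate, that procedure protects the equality nulls. It does not protect the noninferiority null, the gate is not stated, and the comparison is labelled post hoc. It does not give superiority the standing of the named hypothesis.
- **Partial success need not be the likeliest result.** The table shows why: with a 1-point gain and SD 2 to 4, neither part is met in 54% to 82% of trials, and at SD 1 both are met in 62% to 64%. The document gives neither quantity needed to choose among these.
- **The inflated error rate belongs to a rule nobody planned.** It also stays below 5% overall if each part is one-sided 2.5%.
- **An unseen analysis plan may define partial claims.** That would answer a complaint about missing detail. The point here is different: the article states a decision rule, and another rule does everything that one does and more.

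**Conclusion.** The point holds as a free improvement. The combined test is sound and consistent with the aims, but it gives up a confirmatory conclusion on superiority to CBL whenever noninferiority is missed. Under residual SD 1.5 to 4, gains of 2 to 3 points, VCT equal to FFT, 24 per arm and one-sided 2.5% tests, that is about 34% to 81% of trials. Those SDs and gains are assumptions, and outside them the loss can be smaller because either both parts or neither tends to be met. The roughly 1.8-fold error rate is a warning against claiming the parts separately without an order. It is not a property of the plan as written.

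**What to change.** In Statistical Methods, replace the single combined test with a fixed sequence, each step at full alpha:

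1. Test VCT superior to CBL on the ANCOVA-adjusted postintervention OSAT score.
2. Only if step 1 succeeds, test VCT noninferior to FFT with margin 0.675.

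State that success at step 1 alone supports a claim of superiority to CBL with noninferiority to FFT not shown, and that success at both steps supports the combined claim. Match the wording of the abstract and the Objectives section.

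The cost is a few sentences, with no added participants, data or alpha. The one restriction, that noninferiority cannot be claimed without superiority to CBL, is already imposed by the combined test; that pattern occurs in under 3% of simulated trials at gains of 2 to 3 points and about 6% or less at a gain of 1. The Results section says data collection has begun, so the change should be recorded before analysis, through the updated protocol version that the Protocol Amendments section provides for.
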